#### Serious adverse events

A serious adverse event is any untoward medical occurrence or effect that any dose

- results in death,

- is life threatening\*,
- results in persistent or significant disability/incapacity†,
- requires in-patient hospitalization‡ or prolongation of existing hospitalization
- is a congenital anomaly/birth defect in the offspring of a study subject.
- is an important medical event that may jeopardize the patient or may require intervention to prevent one of the other outcomes listed above should be considered serious. (Examples of such treatments are intensive treatment in an emergency room or at home for allergic bronchospasm; blood dyscrasias or convulsions that do not result in hospitalization; or development of drug dependency or drug abuse.)

Although not considered as 'serious adverse events', cancers should be reported in the same way as serious adverse events.

\* Life threatening - definition: An adverse event is life threatening if the subject was at risk of death at the time of the event; it does not refer to an event, which hypothetically might have caused death if it were more severe.

† Disabling/incapacitating - definition: An adverse event is incapacitating or disabling if the event results in a substantial disruption of the subject's ability to carry out normal life functions. This definition is not intended to include experiences of relatively minor medical significance such as headache, nausea, vomiting, diarrhea, influenza, injection site reactions and accidental trauma (e.g. sprained ankle).

‡ Hospitalization: In general, hospitalization signifies that the subject has been detained (usually involving at least an overnight stay) at the hospital or emergency ward for treatment that would not have been appropriate in the physician's office or out-patient setting.

Hospitalization for either elective surgery related to a pre-existing condition, which did not increase in severity or frequency following initiation of the study or for routine clinical procedures (including hospitalization for "social" reasons) that are not the result of an adverse event need not be considered as adverse events and are therefore not serious adverse events.

¶ Routine Clinical Procedure definition: One, which is defined as a procedure, which may take place during the study period and should not interfere with the study vaccine administration or any of the ongoing protocol specific procedures.

N.B. If anything untoward is reported during an elective procedure, that occurrence must be reported as an adverse event, either 'serious' or non-serious according to the usual criteria.

When in doubt as to whether 'hospitalization' occurred or was necessary, the adverse event should be considered serious.

## 8.2 Surveillance period for occurrence of adverse events

All adverse events occurring within one month (minimum 30 days) following administration of each dose of vaccine/ placebo must be recorded on the Adverse Event Form in the subject's CRF, irrespective of severity or whether or not they are considered vaccination-related.

Additionally, all serious adverse events brought to the attention of the investigator during the period starting from the day of performance of the first study procedure for each subject and ending not earlier than six months (minimum 180 days) following administration of the last dose of study vaccine for that subject must be recorded. See 8.8 for instructions for recording and reporting of serious adverse events.

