| CLINICAL INVESTIGATOR + STUDY CENTER  |                           | PD [name]
Clinical Research Center, Kantonsspital Basel
[name]
Ch 4031 Basel
Switzerland                                                                                                                                                                                                                                                                                                                                                                                                                                                                                                                                                                                                                                                                                                                                                                                                          |
| PLANNED STUDY PERIOD + CLINICAL PHASE |                           | October 2003 to October 2004

Phase I                                                                                                                                                                                                                                                                                                                                                                                                                                                                                                                                                                                                                                                                                                                                                                                                                                                                                    |

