 T-cells will not be assessed in groups PEV 301 10 µg and 302 10 µg

a Should be 9 weeks after the 1st vaccination

b must be 2 (+1) days after vaccination

c must be 7 (+2) days after vaccination

d Must be 21 (+5) days after vaccination

e Should be 26 weeks after the 1st vaccination

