## 3 Study Design

This prospective phase I, single centre, randomized, single blind, placebo controlled, dose escalating study will be conducted in 46 healthy adult volunteers. Eligible study participants will be randomized into six groups: PEV 301 10 µg (group A, n = 8) or PEV 302 10 µg (group B, n = 8) or PEV 301 50 µg (group C, n = 8) or PEV 302 50 µg (group D n = 8) or PEV 301 50 µg plus PEV 302 50 µg (group E, n = 8) or virosomes alone (group F, n = 6).

Study participants will be vaccinated three times, i.e. at days 1, 64(+2) and 183(+2) and followed-up 3 times after each vaccination. If any of the study groups does not show any immune response 3 weeks after the 2nd vaccination, no 3rd vaccination will be given to that group, i.e. the study for that group will be terminated 3 weeks after the 2nd vaccination.

Groups C & D (PEV 301 50 µg; PEV 302 50 µg) will be started 5 weeks after the 1st vaccination of groups A, B.

Group E (PEV 301 plus PEV 302) will be started 5 weeks after the 2nd vaccination of groups C and D.

Group F will be distributed and serve as a control in all groups receiving the active product.

The total duration of the study for each participant is 31 weeks, the number of visits is 13.

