## 8 Adverse Events (AEs)

The recording of adverse events is an important aspect of study documentation. It is the responsibility of the investigator to document all adverse events according to the detailed guidelines set out below.

The subjects will be instructed to contact the investigator immediately should the subject manifest any signs or symptoms they perceive as serious during the period extending from performance of the first study procedure up to and including 6 months (minimum 180 days) after the last dose of study vaccine.

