## **10.7 Final analysis**

The final analysis will be performed after evaluation of the data of the 3rd vaccination of groups E and F.

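### The 31-week duration and October 2004 study end precede the close of the 180-day SAE window for all 46 subjects on the planned schedule, and nothing ties the final safety conclusion to that window

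*Protocol*

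**What the plan says.** - **Surveillance.** Section 8.2 sets two windows. For all AEs: "All adverse events occurring within one month (minimum 30 days) following administration of each dose of vaccine/ placebo must be recorded". For SAEs brought to the investigator's attention, recording runs over a period "ending not earlier than six months (minimum 180 days) following administration of the last dose of study vaccine". Section 8 tells subjects to contact the investigator about anything they perceive as serious "up to and including 6 months (minimum 180 days) after the last dose of study vaccine".
- **Duration.** Section 3: "The total duration of the study for each participant is 31 weeks, the number of visits is 13". The synopsis gives the study period as "October 2003 to October 2004", and the flow chart puts the last visit (group E and its two F subjects) in week 42/2004.
- **Last visit.** Footnote d of the Schedule of Assessments: "Must be 21 (+5) days after vaccination". Section 5.2.3 has 22 (+5) days for the same visit. No contact is scheduled after it.
- **Analysis trigger.** Section 10.7: "The final analysis will be performed after evaluation of the data of the" third vaccination of groups E and F. It gives no date, no SAE cut-off and no later safety update.
- **What the analysis must support.** Safety is the primary objective (section 2.1), and the hypothesis in section 10.4 includes that no vaccine-attributable SAE occurs.

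**The concern.** The protocol fixes how long safety is to be watched, how long the study lasts and when it is finally analysed, and these do not line up. A team following section 10.7 as written could close the analysis and conclude on the SAE hypothesis while SAE recording required by section 8.2 is still open for most subjects. Follow-up would be shortest in group E, the only group to receive both components, in a first-in-human study.

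The undefined end of study affects other rules too. Section 8.6 follows non-serious AEs until the end of the study. Section 8.9 caps SAE follow-up at 6 after the last vaccination, with no unit. Section 8.10 treats the study period as running to at least 30 days after the last dose, which is later than the last visit.

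**Working it through.** **1. The protocol's own figures reproduce.** Screening in week -1 plus study weeks 1 to 30 gives 31 weeks. In each cohort the flow chart puts dose 2 nine weeks after dose 1 (day 64), dose 3 at 26 weeks (day 183) and the last visit 21 days after dose 3. The last visit of the E cohort, week 42/2004, is 11 to 17 October if weeks are ISO weeks, which agrees with the synopsis.

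**2. Length needed per subject.** Day 183 + 180 = day 363, and 363 / 7 = 51.9 weeks. The permitted range for dose 3 (days 176 to 187) gives days 356 to 367. The stated 31 weeks is 31 × 7 = 217 days.

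**3. Position at week 42/2004.** Days since dose 3 = 7 × (42 − week of dose 3); days left = 180 − days since dose 3. These do not depend on the week convention; the closing dates assume ISO weeks.

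| Cohort | n | Dose 3, week of 2004 | Days since dose 3 | Days left | Window closes |
|---|---|---|---|---|---|
| A, B and 2 F | 18 | 20 | 154 | 26 | 6–12 Nov 2004 |
| C, D and 2 F | 18 | 25 | 119 | 61 | 11–17 Dec 2004 |
| E and 2 F | 10 | 39 | 21 | 159 | 19–25 Mar 2005 |

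Closed windows: 0 of 46. On 31 October it is still 0 of 46, and the first cohort misses by 6 to 12 days.

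Elapsed share of the required post-dose-3 SAE time at the start of week 42: (18 × 154 + 18 × 119 + 10 × 21) / (46 × 180) = 5,124 / 8,280 = 62%. In the E cohort it is 21 / 180 = 12%. On 31 October, counting from the Monday of each dosing week: (18 × 174 + 18 × 139 + 10 × 41) / 8,280 = 6,044 / 8,280 = 73%.

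**4. Position at the final analysis.** Section 10.7 gives no date, so a lag after week 42 has to be assumed. The flow chart's interim analyses follow the matching visit by 16 − 13 = 3, 22 − 18 = 4 and 36 − 32 = 4 weeks. The days left in step 3 correspond to lags of 26 / 7 = 3.7, 61 / 7 = 8.7 and 159 / 7 = 22.7 weeks.

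- Lag of 3 to 4 weeks (1 to 14 November 2004): some or all of the 18 A/B/F windows may have closed; 18 + 10 = 28 remain open.
- Lag of about 9 weeks: only the 10 E/F windows remain open.
- Lag of about 23 weeks: all windows are closed.

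**5. Departures from the planned schedule.** Dosing on the earliest permitted day (176) closes the first A/B/F windows on 30 October 2004. If a cohort's last dose is dose 2, its window closes on 10–16 July (A/B/F), 14–20 August (C/D/F) or 20–26 November 2004 (E/F).

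**6. The 30-day AE window.** The last visit is 21 to 26 days after dose 3, so 30 − 26 = 4 to 30 − 21 = 9 days remain (3 to 8 days under section 5.2.3). The latest scheduled last-visit day, 213, does not close the gap: it arises from dose 3 on day 187, and that subject's 30 days end on day 217. After doses 1 and 2 the next vaccination visit falls after day 30 and can pick up late events. After dose 3, or after dose 2 in a group stopped early, no later visit does so.

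**The case against.** Four stronger readings are tempting, and the protocol does not support them.

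- **That the final analysis precedes the window for all 46 subjects.** This holds for the stated study end on the planned schedule, not for the analysis. Section 10.7 is an event trigger. At the interim lag the 18 A/B/F subjects are borderline, and the laboratory work in section 10.7.2 (growth inhibition, ELISPOT, clonal T-cell assays) could take longer. A group stopped after dose 2 also closes its window sooner.
- **That the provisions cannot all be met.** A 31-week visit phase followed by passive SAE reporting is workable. Exclusion criterion 1 itself distinguishes the study period from safety follow-up, and sections 8, 8.2 and 8.8 do not tie SAE reporting to visits. For a group stopped early, the SAE window runs from that subject's own last dose, and sections 8 and 8.2 are not cancelled by section 3 calling the study terminated three weeks after dose 2.
- **That SAE data would be lost.** Reporting continues to 180 days. What is missing is the step from those reports into the conclusion.
- **That AE rates per dose become non-comparable in a way that biases the results.** Section 10.6 compares groups on presence or absence of an event in each subject and plans no comparison of dose 1 with dose 3. All groups share the schedule, so a common 4 to 9 day tail does not in itself bias the planned tests.

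The size also depends on the denominator. Counted from dose 1, the elapsed share at the start of week 42 is (46 × 182 + 5,124) / (46 × 362) = 13,496 / 16,652 = 81%. Finally, a data cut-off may be set in an SAP that is not at hand. That would settle the cut-off, but not the durations and windows that the protocol itself fixes.

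**Conclusion.** The point holds in this form. On the planned three-dose schedule, the October 2004 study end and the 31-week duration precede the close of the 180-day SAE window for all 46 subjects. A final analysis run at the section 10.7 trigger would probably precede closure for at least 28 of 46, including all eight in group E. Nothing in the protocol carries later SAEs into the primary safety conclusion. Separately, the 30-day AE window after the last dose outlasts the last visit by 4 to 9 days (3 to 8 under section 5.2.3).

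The count of 28 assumes that the final analysis follows its visit by about the same 3 to 4 weeks as the interim analyses. The calendar dates assume ISO weeks. The 30-day gap needs neither assumption. This should be corrected, but it is mostly a reconciliation of wording and does not invalidate the design.

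**What to change.** - **Section 10.7.** Call the analysis after visit 13 the analysis through visit 13. Make the final statement on the SAE hypothesis conditional on closure of the 180-day window for the last subject, either as the final safety analysis or as a planned SAE addendum.
- **Synopsis and sections 3, 8.2, 8.6, 8.9 and 10.7.** Reconcile these so that the study period and participant duration show the safety follow-up, the end of study is defined for groups stopped early, and the missing unit in section 8.9 is supplied.
- **30-day window.** Reconcile it with the day 21 (+5) visit, and that visit with the 22 (+5) in section 5.2.3. For example, state how AEs between the last visit and day 30 are captured, or report AEs over the window actually observed.

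**Cost.** Protocol wording, and at most one brief contact per subject if that route is chosen. The complete SAE statement comes about five months after the last visit (159 days from week 42/2004), or an addendum is issued.

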### 8.3 Recording adverse events

At each visit/assessment, all adverse events either observed by the investigator or one of his clinical collaborators or reported by the subject spontaneously or in response to a direct question will be evaluated by the investigator. Adverse events not previously documented in the diary card will be recorded in the Adverse Event form within the subjects CRF. The nature of each event, date and time (where appropriate) of onset, outcome, intensity and relationship to vaccination should be established. Details of any symptomatic/corrective treatment should be recorded on the appropriate page of the CRF.

#### 8.3.1 Solicited adverse events

Solicited symptoms are adverse events reported by the subjects, which occur immediately after the injection, or any time between the injection and the 4-day follow-up period.

#### Local (injection site) adverse events

The following solicited adverse events have been reported in similar studies:

- Pain
- Redness
- Swelling

Solicited local adverse events are considered "vaccine-related".

#### General adverse events

This is the first study in men with PEV 301 and PEV 302, therefore, general solicited adverse events related to PEV 301 and PEV 302 will be determined in this study.

As a consistent method of soliciting adverse events, the subject should be asked a non-leading question such as:

"Have you felt different since receiving the vaccine or since the previous visit?"

Adverse events already documented in the CRF, i.e. at a previous assessment, and designated as 'ongoing' should be reviewed at subsequent visits, as necessary. If these have resolved, the documentation in the CRF should be completed. If an adverse event changes significantly in frequency or intensity during a study period, a new record of the event will be started.

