| SAFETY                         |                                                   | 
 
Occurrence of adverse events: self-assessment of local and systemic reactions for 4 days after each vaccination (diary) as well as assessment by investigator during 30 minutes after each vaccination and 2 (+1) days as well as 7 (+2) days after each vaccination.
 
Occurrence of clinically significant hematological and biochemical abnormalities (hematological and biochemical analysis will be carried out at the screening visit (baseline), 7 (+2) and 21 (+5) days after each vaccination).
 
Significant reduction of health status compared to baseline (as assessed by investigator at baseline, i.e. prior to 1st vaccination, during 30 minutes after each vaccination and 21 (+5) days after each vaccination).
 
                                                                                                                                                                                                                                                                                                                                                                                                                                                                                                                                                                                                                                                                                                                                                                                                                                                                                                                                        |

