## 1.5 Benefits and Risks

Volunteers will not benefit directly from participation in this study. However, it is hoped that the information gained from this study will contribute to the development of a safe and effective malaria vaccine. The general risks to participants in this Phase I study are associated with phlebotomy and with vaccination. The volume of blood drawn over the study should not compromise these otherwise healthy subjects. Potential risks include the following:

**Local reactions:** Mild tenderness, bruising, or fainting may result from venipuncture. An inflammatory reaction as manifested by redness, swelling, and/or tenderness may occur at the site of vaccine injection. All these local reactions have spontaneously resolved within weeks.

**Systemic Reactions:** Systemic reactions to immunization could theoretically occur, and include a flu-like illness with low-grade fever, chills and malaise. However, experience to date with other CSP vaccines suggests that if such reactions occur, they resolve in 12 days without therapy or limitation of daily activity. Serum sickness reactions due to deposition of antigen-antibody complexes, or idiosyncratic immune responses not dependent on immune complexes could theoretically develop resulting in damage to organs, such as the liver or kidney. Such immunemediated reactions have not been reported to date after malaria vaccines. Temporary ascending paralysis, the Guillain-Barré syndrome, may occur with any vaccine, although it is very rare.

**Allergic Reactions and Anaphylaxis:** As with any vaccine, allergic reactions are possible. A variety of synthetic and recombinant malaria peptide vaccines have induced systemic allergic responses, e.g., urticaria and anaphylaxis. The allergic reactions occurred after 2-3 vaccinations administered at intervals of 1 month or more, vaccines were formulated with Alhydrogel or QS-21 adjuvants, and high antigen concentrations (200 µg - 2000 µg) were inoculated with each dose. Reactions were occasionally associated with development of antigen-specific IgE antibody.

**Adventitious Agents:** Each lot of vaccine is tested for sterility and for either endotoxin content or pyrogenicity. The formulated product is released for use in humans when the release criteria are met, which suggests that the product is free of known microbial contamination that could infect humans. Nevertheless, the risk of unknown microbe is always present.

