### 5.2.1 Screening of potential study participants

During the Screening Visit (days –7 to -5) the investigator has to check whether potential participants for this study meet the inclusion criteria. Volunteers will not be included if any of the exclusion criteria apply. Volunteers who have signed the Informed Consent Form will undergo complete physical examinations, including vitals signs (blood pressure, pulse, temperature) and body systems (cardiovascular, gastro-intestinal, CNS, ENT, respiratory, urogenital, dermatology). Demographic data will be collected, and a complete clinical history will be recorded, and laboratory tests (including HIV and influenza A titer) and a pregnancy test in female volunteers will be performed. In the event that a subject is tested positive for HIV, he/she will be informed and referred for counseling and treatment. Temperature will also be measured daily by the subject and recorded on the diary card provided.

If materials are provided by a centralized laboratory, it is mandatory that all clinical samples (including serum samples) be collected using exclusively those materials in the appropriate manner. The use of other materials could result in the exclusion of the subject from analysis. The investigator must ensure that his/her personnel and the laboratory(s) under his/her supervision comply with this requirement.

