### 10.2 Primary tests

#### Safety and Tolerability

- Occurrence of local and systemic adverse events
- Occurrence of clinically significant hematological and biochemical abnormalities

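### Section 8.3.1 names no general solicited events and gives diary temperature no rule for becoming an event, so systemic reactions may be recorded less uniformly than local ones

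*Protocol*

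**What the plan says.** The first primary safety item in section 10.2 is "Occurrence of local and systemic adverse events". The two kinds of event are specified differently.

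- **Local events.** Section 8.3.1 introduces pain, redness and swelling with "The following solicited adverse events have been reported in similar studies", and section 8.4 gives each its own 0 to 3 scale.
- **General events.** Section 8.3.1 gives no list. Because this is the first study in humans, "general solicited adverse events related to PEV 301 and PEV 302 will be determined in this study". It continues: "As a consistent method of soliciting adverse events, the subject should be asked a non-leading question such as", followed by one open example question.
- **Expected profile.** Section 1.5 says: "Systemic reactions to immunization could theoretically occur, and include a flu-like illness with low-grade fever, chills and malaise". It then refers to experience with other CSP vaccines.
- **Diary.** The Synopsis describes "self-assessment of local and systemic reactions for 4 days after each vaccination (diary". Section 6.4 tells volunteers to note whatever signs or symptoms they notice.
- **Temperature.** Section 5.2.1, on screening, says: "Temperature will also be measured daily by the subject and recorded on the diary card provided".
- **Definition of solicited.** Section 8.3.1 defines solicited symptoms by timing: immediately after injection or "any time between the injection and the 4-day follow-up period".

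**The concern.** A list of solicited events is an input to data collection. It has to be on the form before the first volunteer is vaccinated, so the study cannot also produce it as a result. Without it, a mild systemic symptom is recorded only if the volunteer thinks to mention or write it, and each volunteer may describe it differently. Local reactions have three named items and fixed grades.

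The sample size in section 10.5 is justified by estimating adverse event frequency in groups of 8, where one or two missed volunteers change the estimate materially. A later analysis plan can change how recorded events are summarised, but it cannot recover symptoms that nobody was prompted to report.

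Temperature is the one objective systemic measure volunteers take at home. If no rule turns a reading into an event, identical readings may be handled differently from one volunteer to the next.

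**Working it through.** **1. Is the reason for having no general list consistent?** The reason given in 8.3.1 is that the products are new in humans. They are equally new for local reactions, yet local items were listed from similar studies. Section 1.5 offers the same kind of basis for general reactions: it names three and cites other CSP vaccines, and section 1.3 says PEV 302 carries a CSP mimotope. The protocol therefore already holds the material for a list.

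**2. By which routes can a systemic event be recorded?**
- The four-day diary, which covers systemic reactions (Synopsis) and is filled in freely (6.4).
- Observation for 30 minutes after each dose, then investigator assessments at 2 (+1) and 7 (+2) days, when the diary is checked and collected (Synopsis, 5.2.3).
- The open question (8.3.1).

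There are several routes, but none has stated general items.

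**3. Where does temperature go?** It is not named in the endpoints (Synopsis, 10.2), the Schedule of Assessments, or the methods (10.6, 10.7.1). The general safety listings in 10.6 and 10.7.1 can include it, and 8.4 sends all non-local events to CTCAE v3.0. The 38°C value in 4.3 and 4.4 governs enrolment and deferral of a dose. No section says when a diary reading is recorded as an event. If temperature is taken on the four diary days after each dose (5.2.1 does not say which days), there are at most 46 × 3 × 4 = 552 readings, fewer if a group stops after dose 2.

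**4. Is a systemic symptom on day 2 automatically related?** By the timing definition in 8.3.1 it is solicited, and 8.5 deems all solicited reactions related. But 8.3.1 states automatic relatedness only for local events, and 8.3.2 has the investigator assess the relationship of systemic signs. The sections do not give one answer.

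**5. Scale.** The planned total reproduces: 5 × 8 + 6 = 46. The protocol gives neither a systemic reaction rate nor a capture share, so both are assumptions here. Recorded rate = true rate × share captured, *s*.

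One group of 8, chance of recording no case:
- True 25%, *s* = 1: 0.75^8 = 0.10.
- True 25%, *s* = 0.5: (1 − 0.125)^8 = 0.875^8 = 0.34.

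Section 10.6 tests event types that occur 10 or more times. Reading this as 10 or more of 46 volunteers, and applying one rate to all groups, the binomial chance of reaching it is:

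| True rate | *s* = 1 | *s* = 0.75 | *s* = 0.5 |
|---|---|---|---|
| 20% | 0.44 | 0.14 | 0.01 |
| 30% | 0.92 | 0.61 | 0.14 |
| 40% | 0.997 | 0.92 | 0.44 |

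With full capture nothing is lost. The table shows sensitivity to the assumption and does not estimate the loss in this trial.

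**The case against.** The strongest reply is that the protocol does collect systemic events, and by more than one route. The diary expressly covers systemic reactions, the investigator checks it and sees the volunteer twice in the week after each dose, and section 8.2 requires every event within 30 days to be recorded whatever its severity or cause. By the timing definition, fever or malaise within the diary window is solicited. Fever is an adverse event under 8.1, is graded by CTCAE v3.0 and is part of the primary endpoint. Tabulation detail may sit in an analysis plan. The diary card is not in the document, so it may already prompt for general symptoms.

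Most of this stands, and it rules out three stronger readings that a reader might infer:
- That systemic events are sought by one open question alone. The diary and the visits contradict this.
- That temperature enters no analysis. It has no named summary, but the safety listings can carry it and fever can be recorded as an event.
- That systemic rates would be under-counted. The protocol gives no capture share, so this is not shown. Section 1.5 also calls these reactions theoretical; it does not predict them.

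The reply leaves three things unanswered: the protocol still postpones the general list to the study's own results, still has no rule linking a temperature reading to an event, and still gives conflicting directions on relatedness. An unseen diary card might remedy the first, but then 8.3.1 should say so.

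**Conclusion.** The point holds as a defect in how data collection is specified. Section 8.3.1 fixes local items and leaves general ones open, although 1.5 already supplies candidates. The systemic part of the primary safety endpoint may therefore be captured less uniformly than the local part. The size is unknown: at the assumed shares of 50% to 75%, a true 30% rate would be recorded as 15% to 22.5%; at full capture there is no loss. The conclusion rests on the protocol text and on the diary card having no general items beyond what the protocol describes. It is an inexpensive improvement to a safety study and does not mean that the planned safety results would be invalid.

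**What to change.** - **8.3.1:** replace the sentence that leaves the general list to the study with the items 1.5 names (fever, chills, malaise), printed as fixed lines on the existing four-day diary card. Keep the open question for everything else.
- **5.2.1:** move the temperature instruction to the description of the diary and state the days it covers.
- **8.4 and 10.6:** state how a diary temperature becomes a recorded event, grade it by the CTCAE v3.0 already adopted, and tabulate the maximum post-dose temperature and its grade by group. Tabulating the maximum keeps low-grade values below the 38°C used in 4.4 for deferring a dose.
- **8.3.1, 8.3.2 and 8.5:** reconcile which solicited events are deemed related and which the investigator assesses. This should be settled together with the new diary lines, since otherwise prompted background symptoms could be counted as vaccine-related by definition.

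The cost is the diary layout and a few sentences, with no extra visit or sample. The downside is that prompting raises background reports in every group, including group F, so the general items should be read against the virosome controls, who number only 6.
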